### Data management

Since all data will be supplied directly by the patients and the assessors through an online interface via a tablet there is no risk of data loss or distortion along the way. Data will be stored encrypted and in unidentifiable form (using participant-numbers) in the server at Glostrup Hospital, University of Copenhagen. Standard missing data analysis will determine whether or not unexpected but missing data due to participant drop-out are random.

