### Feasibility study and power calculation

A feasibility study has been conducted with the aim of testing and evaluating selected methods and instruments for this trial, as well as testing all elements of the planned study (November 2012 to May 2013). The feasibility study included 19 patients with RA with an average daily sitting time at baseline of 10.13 ± 1.7 hours (mean ± SD). The SD for calculation of sample size in the current trial was based on ActivPAL® data from the feasibility study measured as total daily sitting time. We expect a reduction in average daily sitting time of 50 minutes in the intervention group. This estimated reduction in sitting time is based on a US pilot study from 2012 on obese office workers who reduced their daily sitting time by 48 minutes as a result of a behavioral intervention [28]. For a 2-sample pooled *t*-test of a normal mean difference with a 2-sided significance level of 0.05, assuming a common standard deviation of 102 minutes, a sample size of 67 RA patients per group is required to obtain a power of at least 80% to detect a group mean difference of 50 minutes. Enrolling a sample size of 75 in the intention-to-treat (ITT) population per group has a reasonable power (84.7%) to detect a mean difference of 50 minutes (SAS Power and Sample Size, v. 3.1; SAS Institute Inc., Cary, NC, USA).

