### Statistical analysis

The scoring of the standardized questionnaires will be carried out according to the guidelines from instrument developers. All data analyses will be carried out according to a pre-established analysis plan; all analyses will be done applying SAS software (v. 9.3; SAS Institute Inc., Cary, NC, USA). All descriptive statistics and tests will be reported in accordance with the recommendations of the ‘Enhancing the QUAlity and Transparency Of health Research’ (EQUATOR) network: the CONSORT statement [55]. In order to evaluate the empirical distributions of the continuous outcomes, visual inspection will be used to suggest whether the assumption of normality is reasonable. The univariate procedure (PROC UNIVARIATE) statement will be used for summarizing the data. All analyses will be conducted according to the ITT principle; that is analyzing participant outcomes according to the group to which they are randomized, even if some participants do not receive the intervention according to the randomization. We will run the analyses where missing data are imputed by multiple imputation. For sensitivity we will also perform analyses ‘as observed’ analyses where we will not use any missing data imputation. All reported *P*-values and 95% confidence intervals (95% CI) will be 2-sided and will not be adjusted for multiple comparisons. Unless stated otherwise, results will be expressed as the difference between the group means and 95% CI with the associated *P*-values, based on a general linear model (GLM). Data will be analyzed using a one-factor ‘Analysis of Covariance’ (ANCOVA), with a factor for Group, using the baseline value as covariate to reduce the random variation and increase the statistical power.

Proportions will be compared by estimating the risk difference with 95% CIs for each dichotomous outcome; including a Wald-Z-test for the null hypothesis that there is no difference between the proportions.

Secondly, to relate the results to compliance, a ‘per protocol’ analysis will also be used. The ‘per protocol’ population is defined as the patients who have ‘completed’ the intervention to which they were allocated according to the principles described in the intervention section above.

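### The planned drop-out check cannot establish that drop-out is random, and the one missing-data sensitivity analysis named in the article does not test outcome-related drop-out

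*Protocol article*

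**What the plan says.** Three statements in the protocol article bear on missing data.

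- Data management, on what a check of the data will show: "Standard missing data analysis will determine whether or not unexpected but missing data due to participant drop-out are random".
- Statistical analysis, on the main approach: "We will run the analyses where missing data are imputed by multiple imputation".
- Statistical analysis, on sensitivity: as-observed "analyses where we will not use any missing data imputation".

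The analysis model is an ANCOVA with a factor for group and the baseline value as covariate. A per-protocol analysis is added, but its stated purpose is compliance, not missing data. The article gives no drop-out rate and no imputation model. It refers to a pre-established analysis plan, which is not at hand.

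**The concern.** The first statement claims more than any analysis of the collected data can deliver. If it is followed as written, an unremarkable comparison of drop-outs with completers could be reported as showing that the missing data are harmless.

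The sensitivity analysis does not make up for this. Its value lies in changing the assumption that the main analysis depends on. Here the main and sensitivity analyses share most of that assumption, so a reader who sees them agree may take comfort that is not warranted.

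At stake is the primary result, the between-group difference in 16-week sitting time under the intention-to-treat principle. Outcome-related loss is plausible from the article's own description. Patients know their allocation. Only one arm is asked for effort through counselling, personal goals and text reminders. The Background says raised activity is hard to maintain and names pain as a main barrier. The primary outcome needs a monitor worn for seven days and a diary.

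**Working it through.** **1. What observed data can show.** Let R indicate that the 16-week value Y is observed, and let X be the recorded variables.

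- Missing completely at random: P(R | X, Y) = P(R). Dependence of R on X can be seen, so the data can contradict this. Finding no dependence does not confirm it.
- MAR: P(R | X, Y) depends only on what is observed.
- MNAR: P(R | X, Y) still depends on Y where Y is missing.

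Telling the last two apart needs the values of Y that were not collected. No test on the observed data supplies them.

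**2. The plan's own figures.** Inputs from Feasibility study and power calculation: "2-sided significance level of 0.05", "assuming a common standard deviation of 102 minutes", "to detect a group mean difference of 50 minutes". An exact two-sample t-test gives 79.8% power with 66 per group, 80.4% with 67 and 84.7% with 75. The stated 67 per group and 84.7% both reproduce. The step from 67 to 75 leaves room for (75 − 67)/75 = 10.7% loss, although the article states no drop-out rate.

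**3. Bias arithmetic (illustration).** Let p be the share of an arm that is missing, and δ the number of minutes by which its missing patients sit more than a MAR model predicts. Then

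overstatement of the reduction = p(intervention) × δ(intervention) − p(control) × δ(control).

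With departures in the intervention arm only (assumed values):

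| p | δ = 25 min | δ = 50 min |
|---|---|---|
| 5% | 1.25 | 2.5 |
| 10% | 2.5 | 5 |
| 20% | 5 | 10 |

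A true 50 minutes would be read as about 51 to 60. For scale, the unadjusted standard error with 75 per group is 102 × √(2/75) ≈ 16.7 minutes, so these biases are about 1.25/16.7 ≈ 0.08 to 10/16.7 ≈ 0.6 of a standard error.

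The sign can reverse. With 5% and 25 minutes in the intervention arm but 10% and 50 minutes in the control arm, the result is 1.25 − 5 = −3.75, an understatement.

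**4. Do the two named analyses differ when drop-out is informative?** This was simulated with 2,000 trials, 75 per group, SD 102, an assumed baseline-to-follow-up correlation of 0.5, and 20 imputations from a model with group and baseline. The true difference was −50.

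| Drop-out mechanism | Drop-out, control / intervention | As observed | Multiple imputation |
|---|---|---|---|
| Unrelated to outcome | 4.8% / 11.9% | −50.0 | −49.9 |
| Poor responders in the intervention arm leave | 4.8% / 17.6% | −66.2 | −66.3 |

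In the second row the two analyses differ by 0.02 minutes before rounding, while both are about 16 minutes from the truth. That mechanism is deliberately strong: 16.3/0.176 implies a shift of about 93 minutes, beyond the range in step 3. The row shows that the two analyses move together; it is not a forecast of the size of the bias.

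**The case against.** **The analysis plan is not shown.** Tipping points and reference-based imputation are often left to it, and it may contain them. A reader might infer that the trial has no other sensitivity analysis, but the article cannot support that. What can be said is that as observed is the only one the article names, and that it is a weak choice for this purpose. No unseen plan can make the Data management sentence true.

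**Informative drop-out is not stated to be expected.** A reader might infer from the design that it is. The article calls the missing data unexpected and gives no rate or mechanism. Plausible is as far as the text goes.

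**The direction is not established.** A tempting stronger reading is that both analyses inflate the effect. If 10%, 15% or 20% of the intervention arm were missing with no benefit at all, and completers gained 50 minutes, the randomised effect would be 50 × 0.90 = 45, 50 × 0.85 = 42.5 or 50 × 0.80 = 40. Reporting 50 would then overstate it by 11%, 18% or 25%. The arithmetic is right, but it assumes zero benefit in every intervention drop-out and no departure among controls. Flares and pain can cause loss in either arm, and controls are offered only a group session after the last follow-up.

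**The imputation model is open.** Table 1 collects self-reported sitting time at 16 weeks and later, and monitor data at 6 and 18 months. Imputation that uses these could differ from the as-observed result and would reflect missingness that those variables explain. The near-identity in the simulation depends partly on imputing from group and baseline alone. This point stands, but such imputation would still be MAR given those variables.

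**Nothing hinges on the check.** Multiple imputation is planned whatever the check shows, and nowhere does the article say that agreement will be read as robustness. This is true, and it limits the consequence of the faulty sentence to interpretation.

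**Conclusion.** The concern holds in two limited parts. First, the claim that an analysis will determine whether drop-out is random is wrong as written. Second, the only missing-data sensitivity analysis named in the article shares much the same MAR-type assumption as standard multiple imputation. It therefore cannot show whether the primary result withstands drop-out related to the unseen outcome.

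The size and direction of any bias are unknown. The 1.3 to 10 minutes is an illustration that assumes 5% to 20% missing in the intervention arm, a shift of 25 to 50 minutes there, and none among controls. The primary approach and the sample size need no change. This is an inexpensive improvement, not a flaw that invalidates the design.

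**What to change.** - In Data management, replace the claim with a statement that drop-out will be described by arm and by baseline characteristics, and that this cannot establish whether the missing data are random.
- Keep multiple imputation as the primary approach and the as-observed analysis as a supplement.
- Prespecify an MNAR sensitivity analysis for 16-week sitting time. One option is delta-adjusted imputation, with deltas in minutes varied separately in both arms and the tipping point reported, meaning the shift at which the conclusion changes. Reference-based imputation, in which missing intervention patients are imputed from the control arm, can be used instead or as well.

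The cost is a few lines of text and a little more programming on the same imputed data. No extra patients or measurements are needed.

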### Statistical analysis

The scoring of the standardized questionnaires will be carried out according to the guidelines from instrument developers. All data analyses will be carried out according to a pre-established analysis plan; all analyses will be done applying SAS software (v. 9.3; SAS Institute Inc., Cary, NC, USA). All descriptive statistics and tests will be reported in accordance with the recommendations of the ‘Enhancing the QUAlity and Transparency Of health Research’ (EQUATOR) network: the CONSORT statement [55]. In order to evaluate the empirical distributions of the continuous outcomes, visual inspection will be used to suggest whether the assumption of normality is reasonable. The univariate procedure (PROC UNIVARIATE) statement will be used for summarizing the data. All analyses will be conducted according to the ITT principle; that is analyzing participant outcomes according to the group to which they are randomized, even if some participants do not receive the intervention according to the randomization. We will run the analyses where missing data are imputed by multiple imputation. For sensitivity we will also perform analyses ‘as observed’ analyses where we will not use any missing data imputation. All reported *P*-values and 95% confidence intervals (95% CI) will be 2-sided and will not be adjusted for multiple comparisons. Unless stated otherwise, results will be expressed as the difference between the group means and 95% CI with the associated *P*-values, based on a general linear model (GLM). Data will be analyzed using a one-factor ‘Analysis of Covariance’ (ANCOVA), with a factor for Group, using the baseline value as covariate to reduce the random variation and increase the statistical power.

Proportions will be compared by estimating the risk difference with 95% CIs for each dichotomous outcome; including a Wald-Z-test for the null hypothesis that there is no difference between the proportions.

Secondly, to relate the results to compliance, a ‘per protocol’ analysis will also be used. The ‘per protocol’ population is defined as the patients who have ‘completed’ the intervention to which they were allocated according to the principles described in the intervention section above.

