### Intervention and control group

#### Intervention

The intervention includes: 1) Individual motivational counseling including hand-outs of 4 key messages regarding reduction of daily sitting time [38] in combination with 2) Individual Short Text Message Service (SMS) reminders.Individual motivational counseling

The intervention consists of 3 individual motivational counseling sessions (60 to 90 minutes), conducted by one of the project staff (4 nurses or occupational therapists), who have been trained and calibrated in motivational interviewing (MI) techniques [38] for this specific intervention.

Counselors will simultaneously be trained and supervised by a psychologist to ensure that the intervention will be delivered in a similar way based on the theoretical understanding of MI. The first counseling will take place immediately after randomization to the intervention group, the second will be 2 weeks after, and the third 10 weeks after the first counseling (Figure 1). The motivational counseling sessions will take place in an undisturbed room at the hospital.

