#### Control group

The control group will be encouraged to maintain their usual lifestyle during the 16-week intervention period. When the last follow-up examination is completed they will be offered the opportunity to join an information session (in groups) about the principles of the intervention.

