### Primary outcome measure

Change in total daily sitting time in minutes [41,42] from baseline to 16 weeks.

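### The per-protocol analysis meant to relate results to compliance compares self-selected completers with controls, and its criterion is ambiguous for the control arm

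*Protocol article*

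**What the plan says.** The Statistical analysis section makes ITT the rule: "All analyses will be conducted according to the ITT principle; that is analyzing participant outcomes according to the group to which they are randomized". Missing data are multiply imputed, and the model is an ANCOVA "with a factor for Group, using the baseline value as covariate".

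A per-protocol analysis follows, introduced with "Secondly, to relate the results to compliance". Its population is the patients who completed the "intervention to which they were allocated according to the principles described in the intervention section above". No criterion is given for either arm separately.

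The part of the article this points to describes both arms. For the intervention arm it lists process elements: "The intervention consists of 3 individual motivational counseling sessions (60 to 90 minutes") plus SMS reminders. For controls the only content during the 16 weeks is: "The control group will be encouraged to maintain their usual lifestyle during the 16-week intervention period". The primary outcome is "Change in total daily sitting time in minutes" from baseline to 16 weeks.

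**The concern.** The analysis is meant to answer what the counseling does for patients who take it up. Completion is decided after randomisation. Patients are not blinded, and the second and third sessions review each patient's own sitting goals. Someone who is managing to sit less has more reason to keep attending than someone who is not. Dropping non-completers from one arm only therefore removes patients whose counterparts remain in the other arm, and the likely direction is towards benefit.

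The control criterion adds a second problem. Keeping a usual lifestyle overlaps with the primary outcome, because sitting time is part of lifestyle. If someone applied the rule to controls on that basis, selection would be on the outcome itself.

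At stake is the reading of a secondary result: a per-protocol difference could be taken as the effect in compliant patients when part of it comes from selection.

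**Working it through.** **Inputs from the article.** 75 per arm; target difference 50 min; "2-sided significance level of 0.05, assuming a common standard deviation of 102 minutes"; ANCOVA with baseline as covariate. The SD comes from total daily sitting time in the feasibility study (1.7 hours = 102 min), so it is not an SD of change.

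**Assumed, not in the article.** Completion 80%; correlation r of 0.1 to 0.3 between the propensity to complete and reduction in sitting; baseline-to-follow-up correlation ρ of 0.5 to 0.8.

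**The plan's own figures.** A two-sample pooled t-test (noncentral t, difference 50, SD 102) gives 79.8% power at 66 per group, 80.4% at 67 and 84.7% at 75. The stated 67 and 84.7% reproduce. They do not depend on the per-protocol definition.

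**Completers versus all controls, true effect zero, no baseline adjustment.** Keeping the upper 80% of a normal propensity shifts its mean by φ(z)/0.8 with z = 0.842, which is 0.280/0.8 = 0.350 SD. The spurious benefit is r × SD × 0.350:

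- r = 0.1: 0.1 × 102 × 0.350 = 3.6 min
- r = 0.2: 7.1 min
- r = 0.3: 10.7 min

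This takes 102 min as the SD of change, which is exact only at ρ = 0.5, because SD of change = 102 × √(2 − 2ρ).

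**Same contrast with the planned baseline adjustment.** Selection on change also shifts the baseline mean of completers, and ANCOVA removes part of that. The remaining bias is approximately r × 102 × (1 − ρ²)/√(2 − 2ρ) × 0.350:

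| ρ | r = 0.1 | r = 0.2 | r = 0.3 |
|---|---|---|---|
| 0.5 | 2.7 min | 5.4 min | 8.0 min |
| 0.8 | 2.0 min | 4.1 min | 6.1 min |

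A simulation of the planned model (75 per arm, 6,000 trials per setting) agrees: 1.9 to 8.3 min, with type I error from about 5% to 9%. If completion is unrelated to outcome (r = 0), simulated bias is about zero and type I error is 5.1% to 5.6%.

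**Conditional check: only if controls who sat less were removed.** Suppose, with no true effect, controls whose sitting fell by more than 60 min are dropped.

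- SD of change 102 (ρ = 0.5): P(Z < −60/102) = 0.278 removed; the remaining control mean shifts by 102 × φ(0.588)/0.722 = 47.4 min.
- SD of change 64.5 (ρ = 0.8): 17.6% removed; shift 64.5 × φ(0.930)/0.824 = 20.3 min.
- In ANCOVA simulations (4,000 trials per setting) with one-directional cuts of 50, 100 and 150 min, bias ranged from about 42 down to 2 min and type I error from 81% down to 5%.
- Removing controls for a large change in either direction (50 or 100 min) gave bias of about zero.

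**Randomisation-based alternative.** When only the intervention arm can receive counseling, the complier-average causal effect is the ITT effect divided by the proportion receiving it. A zero ITT effect stays zero. An ITT effect of 50 min with 80% receipt gives 50/0.8 = 62.5 min.

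**The case against.** A reader might infer that the plan removes controls who reduced their sitting, so that the per-protocol analysis selects on its own outcome and could manufacture nearly the whole 50-minute target. The article does not support that. It speaks of completing the allocated intervention, it says controls are only encouraged to keep their usual lifestyle, and the abstract describes them as receiving usual care. A control can plausibly complete by staying in usual care without counseling. The reference to the intervention section may even mean only the subsection on the counseling itself. No measure or threshold of control compliance appears. A 60-minute, one-directional cut is therefore a construction, and a literal reading of keeping one's lifestyle would exclude change in both directions. This objection stands, so the 20 to 47 minute figures show only what would follow from one possible reading.

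It is also fair that selection of completers is a familiar limit of any per-protocol analysis, that the correlations are assumed, that ITT is the main analysis, and that operational detail may sit in the analysis plan, which is not shown. These points limit the weight of the finding but do not remove it. The article itself fixes the population as completers and assigns it the job of relating results to compliance. An analysis plan that follows this inherits the unprotected contrast.

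Finally, dividing ITT by the proportion attending all three sessions would overstate the effect if patients who attended one or two sessions also benefited. That is correct, and the definition of compliance below takes it into account.

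**Conclusion.** The concern holds in a limited form. As written, the per-protocol analysis compares self-selected completers with controls. Under no effect it would show roughly 2 to 11 min of spurious benefit: about 2 to 8 min with the planned baseline adjustment and about 4 to 11 min without. This rests on 80% completion and a correlation of 0.1 to 0.3, with completion more likely in patients who reduce their sitting. At zero correlation there is no bias. The size is modest against 50 min.

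Separately, the criterion is ambiguous for controls. One reading would select on the outcome, but the article does not state that reading. The ITT result and the sample size are untouched.

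**What to change.** 1. State that per-protocol status rests on process criteria only: sessions attended in the intervention arm, and no exclusion of controls for lifestyle change or sitting time.
2. Base the compliance statement on a complier-average causal effect, with randomisation as the instrument and baseline sitting time as covariate. Any per-protocol contrast that is kept should be shown beside it.
3. Define compliance as receipt of any counseling session, or model the number of sessions, so that partial attendance does not break the exclusion restriction. State that restriction. Non-compliance should be one-sided, since controls are offered an information session only after the last follow-up.
4. Label the result as supportive of the ITT analysis.

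**Cost.** A few lines of wording and one extra model. Intervention activities are already to be registered for each patient (Cost data), so no new data collection should be needed. The interval is wider: at 80% receipt it is about 1/0.8 = 1.25 times the ITT interval, whereas dropping 20% of one arm (60 versus 75) widens it by only √[(1/60 + 1/75)/(2/75)] = 1.06. With compliance defined as any session, receipt cannot be lower than full completion, so the widening would be no greater than under a three-session definition.
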